### Biomedical outcomes

The primary biomedical outcome is an integrated measure of glucose levels over the previous 4–6 weeks, defined by HbA1c (using a centralised assay to ensure standardisation). The primary endpoint is HbA1c at 12 months, in those entering the trial with HbA1c >7.5% (58 mmol/mol), and HbA1c at 6 months is the secondary endpoint.

Our primary aim is to compare HbA1c between the two arms and we have therefore confined our primary analysis to those with raised A1c values at baseline. We, therefore, excluded those with an HbA1c below 7.5% (58 mmol/mol) when calculating the primary endpoint as these people have less need to reduce their HbA1c.

However, we have included participants with lower A1c values to ensure we can calculate important secondary outcomes part rates of hypoglycaemia, and other biomedical and psychological outcomes. We have estimated the expected proportion of participants with A1c values above 7.5% at 75% of those currently undertaking DAFNE courses based on a national research database.

Other secondary outcomes are the number of participants achieving either an HbA1c <7.5% (58 mmol/mol) or a decrease in HbA1c of ≥0.5% (≥5.5 mmol/mol) which will be calculated at both 6 and 12 months post course. These cut-off points are recognised throughout the diabetes research community as being clinically relevant.^25^ We will also collect and analyse 24-month outcome data (HbA1c and severe hypoglycaemic episodes) and analyse after the main study has closed and been reported based on locally available clinical data which is routinely collected annually in clinical centres.

Other secondary biomedical outcomes will include: Severe hypoglycaemia, as defined by the American Diabetes Association,^26^ denotes severe cognitive impairment requiring external assistance for recovery, both rates and proportion of those affected; Diabetic ketoacidosis, both rates and proportion of those affected; weight; body mass index; blood pressure; lipids; albumin/creatinine ratio.

### Psychological outcomes and process evaluation

#### Quantitative outcomes

Psychological outcomes and process measures will be collected via self-completed postal or online questionnaires at baseline, course completion, 3, 6, 9 and 12 months (see table 1).

The primary psychological outcome is the impact of diabetes on quality of life assessed at 12 months using a 15-domain version of the Audit-Dependent Diabetes Quality of Life Questionnaire.^27^

Additional psychological constructs are assessed with validated questionnaires and study-specific individual items, based on: existing knowledge about their association with the trial’s primary biomedical outcome (HbA1c) and primary psychological outcome (diabetes-specific quality of life), including the findings of the YourSAY survey^28^; previous work with the DAFNE intervention, and the theoretical framework underpinning the DAFNE*plus* intervention development and possible treatment mechanisms.^19 29 30^

#### Qualitative outcomes

Interviews will be undertaken with a subset of participants randomised to the intervention at baseline, course completion, 3 months and 12 months (figure 1) to explore how key elements of the intervention influence and inform changes to, and maintenance of, key self-management behaviours over time. Facilitators will be interviewed from across the intervention sites to explore their experiences of intervention delivery and their views about the training, resourcing and support staff would need to deliver DAFNE*plus* in routine care.

#### Fidelity assessment

We will explore fidelity of delivery using two methods to assess the extent to which the intervention content specified in the DAFNE/DAFNE*plus* manuals is delivered as intended: self-report checklists completed by educators/facilitators, and objectively analysed delivery from session audio recordings. Fidelity of delivery will be assessed in standard DAFNE as well as DAFNE*plus* in order to assess any loss of treatment differentiation and potential contamination between the two arms.

Self-report checklists: Facilitators will complete checklists after each session. Each checklist lists the components intended to be delivered in each session (according to the manual). These components correspond to different BCTs. Each component will be rated as fully, partially or not delivered, with space for additional comments. The proportion of intended components rated as partially/fully delivered by educators/facilitators will be calculated, with <50% of intended content delivered classified as low fidelity; 51%–79% as moderate fidelity, and 80%–100%’ as high fidelity.^31^
Objectively analysed delivery: A subsample of group course sessions in both arms will be audio-recorded and transcribed verbatim. Transcripts will be coded into component BCTs using an established taxonomy.^20^ BCTs identified in each session transcript will be compared with corresponding section of the intervention manual that specifies which BCTs are intended to be delivered in that session. Fidelity will be calculated in terms of the percentage of manual-specified BCTs delivered as intended. Additional BCTs delivered that are not specified in the curricula will also be noted.

Detailed plans for the process evaluation are in online supplemental material 2.

10.1136/bmjopen-2020-040438.supp2Supplementary data

### Health economic outcomes

Table 1 details the health economic data collected in the trial. In addition, data collected from the DAFNE*plus* website will be used to cost the intervention. The analysis population for the health economic analyses will include all trial participants, as it is important that the analysis of health economic data includes all participants who would be eligible to receive DAFNE*plus* (if it were to be implemented). In line with the statistical analysis, we will conduct subgroup analyses in participants with an HbA1c ≤7.5% and >7.5% (58 mmol/mol).

Two health economic analyses will be conducted, a primary long-term analysis using the Sheffield T1D Policy Model and a secondary analysis of the data collected in the trial. All health economic analysis will compare the incremental cost-effectiveness ratio of DAFNE*plus* versus DAFNE to standard National Institute for Health and Care Excellence thresholds to determine cost-effectiveness.^32^ See online supplemental material 3 for detailed plans for the economic evaluation.

10.1136/bmjopen-2020-040438.supp3Supplementary data

### Safety outcomes

#### Adverse events

Study centres are only required to report as adverse events episodes of diabetic ketoacidosis and severe hypoglycaemia which while not requiring admission to hospital have been noted by either the participant or their relative/partner etc. These will be recorded on the data collection form and database.

#### Reporting

We do not anticipate many Serious Adverse Events related specifically to DAFNE*plus* or standard DAFNE but will report any which are deemed related to the study intervention and or are unexpected to the Sponsor and the REC in line with best practice.

### Sample size

It is expected that there will be 882 patients referred for DAFNE courses within the 15-month recruitment window and of these it is expected 75% (662 patients) will be recruited, equivalent to 47 participants at each of the 14 centres. From current DAFNE data, a further 25% are expected not to meet the primary analysis population criteria of baseline HbA1c greater than 7.5% (58 mmol/mol), leaving 497 participants. Finally, we anticipate 15% of participants to be lost to follow-up by the 12-month stage, therefore giving a primary analysis population of 422 participants. The sample size takes into account the design effect associated with the cluster design of the study. With an intracluster correlation coefficient (ICC) of 1.5% (from previous DAFNE data) and 30 participants per cluster (422 participants over 14 centres) the design effect is 1.435 leaving the effective total sample size of n=294 participants (n=147 per arm).

Using a two sample comparison of mean HbA1c at the 12-month follow-up with two-sided alpha of 5%, a correlation of 0.5 between baseline and final values and a SD of 1.45 (from previous DAFNE data), the trial sample gives 92% power to detect a 0.5% difference in HbA1c (the minimum clinically important difference) between the two treatment groups in the study.

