**Methods and analysis:**

A pragmatic cluster randomised controlled trial in adults with T1D, delivered in diabetes centres in National Health Service secondary care hospitals in the UK. Centres will be randomised on a 1:1 basis to standard DAFNE or DAFNE*plus*. Primary clinical outcome is the change in HbA1c and the primary endpoint is HbA1c at 12 months, in those entering the trial with HbA1c >7.5% (58 mmol/mol), and HbA1c at 6 months is the secondary endpoint. Sample size is 662 participants (approximately 47 per centre); 92% power to detect a 0.5% difference in the primary outcome of HbA1c between treatment groups. The trial also measures rates of hypoglycaemia, psychological outcomes, an economic evaluation and process evaluation.

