### Random allocation

On recruitment of centres and following ethical approval, the participating centres will be randomised on a 1:1 basis to control or the intervention arm of the trial by the trial statistician. As there are numerous stratification variables that have been identified as clinically important and the small number of randomising centres, a covariate constrained methodology^24^ will be employed. The centres will be matched on the number of patients within the centre, number of educators within the centre and number of previous DAFNE courses delivered (as a marker of centre experience) to balance centres between the two arms of the trial.

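### The stated 92% power uses the reference distribution of 294 independent observations; with 14 randomised centres (12 degrees of freedom) the same inputs give about 88%

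*Protocol article*

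**What the plan says.** All the planning figures are in the Sample size section of the protocol article. It expects 422 participants in the primary analysis, about 30 in each of 14 centres, with an intracluster correlation of 1.5%. From these, "the design effect is 1.435 leaving the effective total sample size of n=294 participants (n=147 per arm"). Power is then taken from a two-sample comparison of means with "two-sided alpha of 5"%, "a correlation of 0.5 between baseline and final values" and "a SD of 1.45 (from previous DAFNE data"). The conclusion is that "the trial sample gives 92% power to detect a 0.5% difference in HbA1c (the minimum clinically important difference"). The abstract carries the same claim: "92% power to detect a 0.5% difference in the primary outcome of HbA1c between treatment groups".

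Random allocation says that centres are randomised 1:1 and gives their small number as one reason for covariate-constrained randomisation. It adds that "The centres will be matched on the number of patients within the centre, number of educators within the centre", together with the number of earlier DAFNE courses. Statistical analysis specifies linear regression fitted by generalised estimating equations (GEE), adjusted for baseline HbA1c and further covariates, and refers to a separate statistical analysis plan.

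**The concern.** A design effect corrects the variance of the treatment comparison. It does not correct the distribution against which the test statistic is judged. Treatment varies only between centres, so the relevant variance is estimated from 14 centre-level units. In a plain two-arm comparison that leaves 14 − 2 = 12 degrees of freedom. The two-sided 5% critical value is then 2.179, not 1.96. The Sample size section makes no allowance for this, although Random allocation recognises that there are few centres.

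The stated power of the main comparison is what is at stake. A reader who meets a null result will use the 92% to judge how likely it was that a real 0.5% difference was missed. If power is 88%, that chance is about 12%, not 8%, which is half as large again.

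**Working it through.** **Inputs, all from the Sample size section unless noted.** Analysed participants 422; centres 14 (7 per arm, from the 1:1 ratio under Random allocation); 30 per centre; ICC 0.015; SD 1.45; baseline–final correlation 0.5; difference 0.5; two-sided alpha 0.05.

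**Step 1: reproduce the plan's figure.**
- Design effect: 1 + (30 − 1) × 0.015 = 1.435.
- Effective n: 422 / 1.435 = 294, or 147 per arm.
- Baseline-adjusted SD: 1.45 × √(1 − 0.5²) = 1.2557.
- Standard error: 1.2557 × √(2/147) = 0.1465.
- Noncentrality: 0.5 / 0.1465 = 3.414.
- Power, normal reference: Φ(3.414 − 1.96) = 92.7%.
- Power, noncentral t with 294 − 2 = 292 df: 92.5%.

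Both agree with the stated 92%. Without the baseline adjustment the normal formula gives 84.0%, so the plan's method is identified as the baseline-adjusted one.

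**Step 2: change only the reference distribution.** Keep noncentrality 3.414 and use 12 df, critical value 2.179.
- Power, noncentral t with 12 df: 87.9%. A simulation of centre means with these inputs gave 88.0%.
- Type II error: 100 − 87.9 = 12.1%, against the implied 100 − 92 = 8%.
- Noncentrality needed for 92% power on 12 df: 3.671. Detectable difference: 3.671 × 0.1465 = 0.538, about 0.54% HbA1c.

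**Step 3: what it takes to keep 92%.** Suppose the statistic has 12 df but is compared with 1.96.
- Power: P(T > 1.96) for noncentral t with 12 df and noncentrality 3.414 is 91.7%.
- Type I error: 2 × P(t on 12 df > 1.96) = 7.4%.

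The stated power is therefore nearly recovered, but not at a 5% alpha.

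**Step 4: sensitivity to unequal centre sizes.** The article gives no coefficient of variation (CV) of analysed centre size, so the CVs here are assumptions. Design effect = 1 + ((1 + CV²) × 30 − 1) × 0.015, with 12 df.

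| Assumed CV | Design effect | Effective n | Power |
|---|---|---|---|
| 0 | 1.435 | 294 | 87.9% |
| 0.2 | 1.453 | 290 | 87.5% |
| 0.4 | 1.507 | 280 | 86.3% |
| 0.6 | 1.597 | 264 | 84.4% |

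**Step 5: sensitivity to the degrees of freedom.** If centre-level covariates enter the model, fewer than 12 df remain. At noncentrality 3.414, 10 df gives 86.7% and 9 df (all three matching factors) gives 85.8%, before counting any precision that those covariates might add.

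**The case against.** Several points can be made for the plan.

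- **The figure is not a slip, and clustering is not ignored.** This stands. A reader might infer that centres were treated as if they did not matter. The Sample size section deflates 422 to 294 for clustering, and the analysis is by GEE. Every printed step is correct by the usual design-effect method. The fault lies only in the reference distribution applied afterwards.
- **The test's standard error and degrees of freedom may be set in the statistical analysis plan.** This stands as far as type I error goes. A reader might infer that the trial will have an inflated error rate. The article does not say that the GEE analysis is uncorrected, so that charge is conditional. It does not rescue the 92%: with a correction, power is about 88%; without one, alpha is not 5%.
- **The closed form may be slightly pessimistic.** A simulation of GEE with a Kauermann–Carroll standard error and 12 df gave 88.9% for equal centres. That is still about 3 points below 92%.
- **Planning inputs are uncertain.** On 12 df, 92% would be reached with an ICC of about 0.008 or a correlation of about 0.59. Matching and extra covariates might also add precision. These gains are not quantified in the article, and covariates may cost degrees of freedom. The claim concerns the inputs actually stated.
- **Nothing shows how unequal the centres will be.** This stands. The matching variable is the number of patients at the centre, not the number analysed in the trial. A reader might infer a definite lower power, such as 86%; the article supports only the direction.

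**Conclusion.** The point holds in a limited form. On the article's own inputs, power at a true two-sided 5% alpha is about 88% (87.9%), some 4 points below the stated 92%. This assumes 7 centres per arm, equal analysed centre sizes, 12 df and no centre-level covariates. Unequal sizes would lower it further by an amount the article does not allow one to fix.

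The consequence is modest. Power stays above 80% at every assumed CV shown, and the article names no target power that would be missed. A reader might conclude that the trial is underpowered or too small; the figures do not support that. What is wrong is a stated operating characteristic, given in two places, that cannot hold together with the stated alpha.

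**What to change.** In the Sample size section and the abstract, restate the power for a 0.5% difference as about 88%. In the Sample size section, say that it is calculated with a t reference on 12 between-centre degrees of freedom and assumes equal centre sizes. Add that unequal analysed centre sizes would reduce it, and show this only as a sensitivity range with the CVs labelled as assumed (for example 87.5%, 86.3% and 84.4% at CVs of 0.2, 0.4 and 0.6).

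Check that the small-sample handling of the GEE analysis in the statistical analysis plan matches the basis of the restated power.

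The cost is a text correction in two places and a stated power about 4 points less favourable. Neither the number of participants nor the number of centres needs to change.

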### Statistical analysis

The primary analysis population will be participants that had an HbA1c greater than 7.5% (58 mmol/mol) at baseline and the analysis will be completed on an intention-to-treat (ITT) basis. This primary analysis is to assess the difference between the two treatment groups on the mean HbA1c at 12 months which will be completed using a multiple linear regression model with coefficients estimated using generalised estimating equations to account for the clustering design. A 95% confidence interval for the difference between the two treatment groups will be presented. Appropriate covariates will be included in the model, along with the participant’s baseline HbA1c, to adjust the treatment effect accordingly.

The secondary analysis population is all consenting participants in the trial and analysis will again be completed on an ITT basis. This population will also be used to assess the difference in psychological outcomes between the two treatment groups using the same model as for the primary analysis.

A full statistical analysis plan has been written and was circulated to the TMG and TSC before being signed-off. This is available in online supplemental material 5. All analyses results will be reported according to the revised Consolidated Standards of Reporting Trials 2010 statement for cluster RCTs.^33^

10.1136/bmjopen-2020-040438.supp5Supplementary data

### Data collection and management

Case report forms will be completed by DAFNE facilitators/educators at each study visit. Follow-up questionnaires will be self-completed by participants at each follow-up point. Participants will be allocated a unique identification number to identify them throughout the trial.

Plans to promote retention and follow-up of all trial participants include research appointments being scheduled and followed up by their clinical teams at 6 months and 12 months. Overdue questionnaires are followed-up with an email reminder and then telephone call from CTRU. All participants received email newsletters to update them on trial progress.

Data will be entered onto the DAFNE*plus* database on CTRU’s secure online system, hosted on University of Sheffield servers. Access is restricted such that users can enter and view only information required to perform their role.

Identifiable data will be shared with CTRU and the supporting study team and DAFNE*plus* website teams. Consent will be obtained from the participant for this to occur. Data will be stored securely on access-restricted network drive folders in accordance with CTRU standard operating procedures (SOPs).

All consent forms and questionnaires will be kept in a locked filing cabinet in a secured area and will be retained for a minimum of 5 years after study completion, in accordance with the sponsor’s archiving requirements. Sheffield CTRU may request consent forms to be sent from the research site to the CTRU via post or email as part of remote monitoring procedures.

The nature, frequency and intensity of trial monitoring will be outlined in the site monitoring plan, which will be devised in accordance with CTRU SOPs.

### Patient and public involvement

In addition to the patient representation on the trial oversight committees, this trial is supported by a patient advisory group who have and will continue to meet regularly during the conduct of the trial (and the wider programme grant). Patient input has been sought throughout on the trial and intervention design, the informational material to support trial conduct and patient burden.

### Trial oversight committees

Two oversight committees have been established to oversee the conduct of this trial— the TSC and TMG, the composition of each is listed at the end of this paper. A Data Monitoring and Ethics Committee has not been convened, on the grounds that the study is low risk, in line with CTRU SOP GOV003. This has been approved by the Sponsor and TSC.

## Ethics and dissemination

The RCT was not initiated until the protocol, informed consent forms and participant information sheets received approval from the Research Ethics Committee, the Health Research Authority and local Capacity and Capability is confirmed by the respective NHS Research and Development departments. MHRA (Medicines and Healthcare products Regulatory Agency) approval was not required for this study.

The RCT is being conducted in accordance with the ethical principles that have their origin in the Declaration of Helsinki^34^; the principles of GCP, and the UK Framework for Health and Social Care Research.^35^

Outputs from the trial will be generated in accordance with the communication and dissemination strategy. A number of academic outputs will be produced as the data are analysed from the trial. Journals will be selected based on the highest possible impact. Other stakeholder-specific outputs in relevant formats will also be produced for commissioners, third sector and user advocacy organisations.
